|  | hot by means of the thermotest between the 2 groups of patients (FR vs SM):   1. before and after each session of FR vs SM at V1 and V4 2. before and after overall RP or MS support between V1 and V4 3. Compare the consumption of analgesics using a record book of analgesic treatments throughout the study, between the 2 groups of patients (FR vs SM). 4. To compare pain acceptance with CPAQ-8, anxiety and depression with HAD, before and after management between the 2 groups of patients (FR vs SM). 5. To determine if there are biomarkers of the effect of RP on brain activity using fMRI before and after management between the 2 groups of patients (FR vs SM). 6. To assess whether there are personality traits that modulate the analgesic response in the 2 groups of patients (according to the results obtained in the TCI personality test) |
| --- | --- |

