## RESEARCH HYPOTHESES AND EXPECTED RESULTS

There is no research on the subject at this time.

We hypothesize that FR will have an effect on pain in patients with Parkinson's disease. Reflexology acts on physical and emotional health, we believe that management with FR could improve chronic pain, anxiety and depression and reduce the use of analgesics in this population.

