## SECONDARY OBJECTIVES

The secondary objectives are:

1. To compare the number of patients with at least 30% improvement in pain on VAS after management between the 2 groups of patients (FR vs SM).
2. To compare the kinetic variation in the analgesic effect of a 4-session PR treatment on the intensity of chronic pain measured by a Visual Analogue Scale (VAS) during management between the 2 groups of patients (FR vs SM).
3. Comparing the variation in chronic pain using King's Parkinson's disease Pain

Scale (KPPS) and the Brief Pain Inventory (BPI), and the Primary Parkinsonian Pain Diagnostic Questionnaire (3PDQ) before and after the overall management between the 2 groups of patients (PR vs. MS).

1. Compare the evolution of the subjective nociceptive threshold and the tolerance to heat using the thermotest between the 2 groups of patients (FR vs SM):

a) before and after overall support between V1 and V4

1. Compare analgesic consumption using a diary of analgesic treatments throughout the study, before and after treatment between the 2 groups of patients (FR vs SM).
2. To compare pain acceptance with CPAQ-8, anxiety and depression with HAD, before and after management between the 2 groups of patients (PR vs. MS).
3. To determine if there are biomarkers of the effect of RP on brain activity using fMRI before and after management between the 2 groups of patients (RP vs MS).
4. To assess whether there are personality traits that modulate the analgesic response in the 2 groups of patients (according to the results obtained in the TCI personality test)

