From the Intensity-Response curve, we will be able to determine the temperature for which the VAS was equal to 75%. This temperature will then be applied twice at five-minute intervals to the patient, who will have to orally express his tolerance threshold (which corresponds to the time before the stimulation becomes unbearable).

1. Consumption of analgesics by means of a collection booklet throughout the study (collection of the prescribed treatment and dosage).
2. At the deltas of the following scores, before and after global management:
   - CPAQ-8 pain acceptance test *[McCracken 2004]*. This self-questionnaire assesses the acceptance of chronic pain via 8 statements. Each item is rated between 0 (never true) and 6 (always true).
   - of the HAD scale *[Lépine 1985]*. It is a self-questionnaire to screen for anxiety/depressive disorders. Patients answer 14 questions: 7 about anxiety and 7 about depression. It is an assessment that measures mild to moderate depression in PPs *[Schrag 2007].*
3. Comparison between the structural and activation maps of brain networks in order to identify biomarkers of the management of brain activity. The modulation of brain activity will also be assessed by means of a map of correlation coefficients representing the strength of connectivity between the different brain networks and regions of interest, obtained from functional MRI sequences at rest, [after – before] care. The main MRI sequences performed will be resting state acquisitions (resting functional imaging) and anatomical imaging (i.e. T1 imaging).
4.
[figure not shown]
Comparison between the 2 groups of patients of their analgesic response according to their personality profile.

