### Other treatments/procedures

Analgesic drugs are also authorized regardless of their pharmacological class. We will thus be able to observe the variation in the consumption of these analgesic drugs during the study. A treatment collection booklet will be provided to the patient.

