4. For the subjective pain perception threshold to heat and heat tolerance. We will perform the same analyses as the primary outcome as these are quantitative scores. 5. For the consumption of analgesics, which will be considered as several qualitative variables (e.g. taking paracetamol yes/no, aspirin taking yes/no), we will compare the proportion of patients taking each analgesic between the 2 groups by means of Chi2 tests.
5. The analyses regarding the CPAQ-8 score will be the same as those for the primary objective as it is a quantitative score. As the anxiety and depression scores of the HAD scale are quantitative variables, they will be analysed in the same way as the primary outcome.
6. As imaging results are quantitative variables, we will analyze them in the same way as for the primary purpose.
7. Personality profile results will be analyzed using a nonparametric Wilcoxon Mann Whitney test

For the study as a whole, the significance threshold is set at 0.05 (bilateral).

The statistical analysis will be conducted by [name] from the MeDatAS – CIC – CHU Toulouse team. Analyses will be conducted using SAS analysis software version 9.4 or later.

All analyses of neuroimaging data will be carried out within the ToNIC unit (Inserm/UPS UMR1214):

- the structural and activation images obtained in MRI for each subject will be normalized and smoothed using the Statistical Parametric Mapping ((SPM) software Wellcome Department of Cognitive Neurology, University College, London, UK).
- The resting state images fMRI will be analyzed using a model-dependent method called "seed-tovoxels" using the Conn software version 18b (https://www.nitrc.org/projects/conn). The seeds will be determined according to anatomical atlases to identify the brain areas of interest (default mode network, sensorimotor network). The connectivity between these seeds and the rest of the brain voxels will be explored.

These images will then be used to perform a t-corrected test for multiple comparisons to compare the cards [after – before] support. Thus, the intensity and size of the synchronous activity of brain areas functionally connected to the areas of interest of the reflex zones stimulated on the foot can be determined. Areas of interest are defined anatomical areas in known and classic stereotactic spaces in neuroimaging.

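### The analgesic objective asks for a before/after comparison between arms, but the planned per-drug yes/no test uses neither dosage nor change from baseline

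*Protocol*

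**What the plan says.** Section 3 (Secondary objectives) sets the task: "Compare analgesic consumption using a diary of analgesic treatments throughout the study, before and after treatment", between the FR and SM arms. The summary (section 1) words the same objective without the before/after element: "Compare the consumption of analgesics using a record book of analgesic treatments throughout the study, between the 2 groups of patients (FR vs SM").

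Section 4 (Secondary outcomes) defines what the booklet holds: "collection of the prescribed treatment and dosage". Section 9 (Inclusion visit) records the analgesics in progress at V1, so a starting point exists. Section 8 allows analgesics of every class and gives the reason: "We will thus be able to observe the variation in the consumption of these analgesic drugs during the study". Section 2 (Research hypotheses) expects that FR "could improve chronic pain, anxiety and depression and reduce the use of analgesics in this population".

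Section 11 (Statistical methods used) then treats consumption as several qualitative variables, one per drug, each coded taken or not taken, and "we will compare the proportion of patients taking each analgesic between the 2 groups by means of Chi2 tests". It states no time point. The summary adds two general rules for qualitative variables: Fisher replaces Chi2 when an expected count is below 5, and McNemar serves before/after comparisons.

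**The concern.** The objective concerns change in consumption, and the data include dosage, but the test looks only at whether a drug is taken. For a patient on long-term analgesics, taking the same drug at a lower dose is a plausible form of benefit, and the yes/no variable cannot register it. Nor does the between-arm test use the patient's status at V1, so it does not compare change.

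The other secondary measures that section 11 treats as quantitative scores (KPPS, BPI, 3PDQ, heat threshold and tolerance, CPAQ-8, HAD) follow the primary method, a change from baseline compared between arms. Analgesic consumption is an exception although its section 3 objective explicitly asks for before and after.

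Reduced analgesic use is one of the trial's hypothesised benefits, and the data are meant to support the design of a larger study. Analgesics are also unrestricted, so a change in their use that differs between arms is relevant background to any VAS difference.

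**Working it through.** **Plan's own figure.** The Protocol gives no power or sample size for this outcome. The only figure needed is the planned 15 patients per arm (section 11, sample size).

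**Step 1: what each section supplies or uses.**

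| Place | Dosage | Baseline or change | Between-arm comparison |
| --- | --- | --- | --- |
| Objective, section 1 | not named | not named | yes |
| Objective, section 3 | not named | before and after | yes |
| Outcome, section 4 | collected | booklet runs throughout the study | yes |
| Inclusion visit, section 9 | not specified | analgesics in progress at V1 | – |
| Purpose, section 8 | – | variation during the study | – |
| Test, section 11 | not used | not used | yes, takers per drug |
| McNemar rule, section 1 | not used | before/after, yes/no | no |

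No row that describes a test uses dosage. No row combines change with a comparison between arms, which is what section 3 asks for.

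**Step 2: rejection rate under a pure dose reduction.** Suppose FR patients lower their dose and nobody stops or starts a drug. The proportion of takers p is then the same in both arms, and the null hypothesis of the yes/no test is true whatever the size of the reduction. With n = 15 per arm, the rejection rate is the sum over a, b = 0…15 of

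Bin(a; 15, p) × Bin(b; 15, p) × 1[test p-value for a/15 vs b/15 ≤ 0.05].

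The Protocol gives no prevalence of use, so p is an assumption:

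| Assumed p in both arms | Chi2 (uncorrected) | Fisher |
| --- | --- | --- |
| 0.60 | 0.049 | 0.016 |
| 0.50 | 0.046 | 0.017 |
| 0.30 | 0.055 | 0.017 |

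The result hardly depends on p: about 2% to 5%, no more than with no effect at all.

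**Step 3: is the information in the data?** An illustrative simulation (4,000 runs, 15 per arm) compared Mann-Whitney on relative dose change with Fisher on yes/no in the same patients. It assumed a standard deviation of relative dose change of 0.4 among users, the same expected share of users in both arms, and nobody stopping a drug.

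| Assumed share of users | Mann-Whitney, FR dose halved | Mann-Whitney, FR dose −30% | Yes/no (Fisher), either case |
| --- | --- | --- | --- |
| 100% | 0.89 | 0.48 | 0.00 |
| 70% | 0.64 | 0.29 | 0.02 |
| 50% | 0.45 | 0.21 | 0.02 |

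Dosage therefore carries information that the yes/no coding discards. Even so, at this sample size a moderate reduction is detected in fewer than half of runs.

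**The case against.** The strongest replies are these.

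- **The objective does not name dose, and the summary version does not name before/after.** This is true, and under the summary wording a between-arm comparison of takers is a fair reading. Section 3 nevertheless asks for before and after, and section 4 makes dosage part of the outcome. The two wordings need reconciling in any case.
- **McNemar is planned for before/after comparisons of qualitative variables.** This stands in part. A reader might infer that no change over time can be detected at all. The documents do not support that, because starting or stopping a drug within one arm can be tested. What is missing is a comparison of change between arms, and any use of dose.
- **Fisher covers small counts.** This stands fully. A reader might infer that Chi2 will be run on counts too small for it, but the summary provides for that case.
- **Randomisation protects the comparison.** This stands. A chance imbalance in users at baseline falls within the error rate of the test and is not a bias.
- **Low power reflects a pilot with 15 per arm.** This stands for patients who stop a drug completely. With an assumed 60% vs 30% of takers, exact power is 0.37 (Chi2) or 0.23 (Fisher). That is mainly a matter of sample size and is not counted here against the yes/no coding.
- **The time window could be set in a statistical analysis plan.** This is accepted, and the missing time point alone is no finding. The variable and the test, however, are fixed in section 11.
- **Days of use are not lost by the analysis.** This is correct. The booklet is described as recording the prescribed treatment, so actual intake may never be captured. That is a matter of data collection.

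**Conclusion.** The mismatch is real. The plan collects dosage and an inclusion record of analgesics, promises to observe variation, and asks in section 3 for a before/after comparison between arms. It then fixes a test that uses neither dosage nor change. For a pure dose reduction, the rejection rate stays at about 2% to 5% at 15 per arm. That range assumes equal proportions of takers and that nobody starts or stops a drug. The conclusion that the test cannot see a dose reduction needs no prevalence figure.

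A reader might go further and infer that a better analysis would settle whether analgesics explain a VAS difference. The documents do not support this: with 15 per arm, a non-significant comparison of change would not exclude it. The point concerns one secondary outcome of an exploratory trial. It leaves the primary test untouched, but it should be corrected before any statement about reduced analgesic consumption is made.

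**What to change.** 1. Keep the per-drug yes/no proportions as description.
2. From the V1 record and the booklet over a stated window before V5, classify each patient's overall analgesic use as decreased, unchanged or increased. A drug stopped counts as a decrease and a drug started as an increase. A rule for mixed changes is set in advance and applied blind to arm. This avoids a percentage of baseline dose, which is undefined for a non-user who starts a drug, and it avoids summing doses across drug classes. It also needs no diary before consent at V1.
3. Compare this ordered change between arms with the Mann-Whitney test already planned for the primary outcome.
4. Make sure that dosage is part of the V1 record, and have the booklet record intake actually taken as well as what is prescribed.
5. Reconcile the objective in the summary with the one in section 3.

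If the sponsor does not want this, narrow the section 3 objective and the section 8 statement to the proportion of takers, and draw no conclusion about reduced consumption.

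Cost: one classification rule, a small change to the booklet and a little programming. The measure is coarse and its power will be limited at this size. The Mann-Whitney figures in the working are for relative dose change and do not carry over to it.

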| **DURATION OF THE SEARCH** | Length of Inclusion Period: 2021 – 2023  Duration of participation of each participant: 12 weeks Total duration of the research: 3 years |
| **ANALYSIS**  **STATISTICS OF**  **DATA** | Descriptive, mean, standard deviation and extent or median and interquartile analysis will be presented for quantitative variables. For qualitative variables, it will be a question of number and percentage.  For comparative analyses between the 2 groups:   - The non-parametric Wilcoxon Mann-Whitney test will be performed for quantitative variables - The nonparametric Wilcoxon test for paired data will be used for before-and-after comparisons for quantitative variables - The Chi2 test (or Fisher if theoretical < 5) will be performed for the qualitative variables - The McNemar test will be used for before-and-after comparisons for qualitative variables. |
| **EXPECTED BENEFITS** | To date, it is clear that very few good quality studies have been carried out on the subject. Here we propose to scientifically and rigorously evaluate foot reflexology in order to reach reliable conclusions in pain in Parkinson's patients. The challenge is to provide concrete help to Parkinson's pain patients and to enable doctors to recommend this type of care in an informed manner. |

*in ON condition; that is to say, at least one hour after taking the anti-parkinsonian treatment for the treatment to be fully effective.

AbstractThis research has been registered in http://www.clinicaltrials.gov/.

Exploratory study of the impact of foot reflexology on chronic pain in parkinsonian patients. University Hospital Toulouse is the sponsor of this research.

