## METHODS FOR RANDOMIZATION

Patients will be randomized into two groups in a 1:1 ratio, the experimental group that will receive the FR sessions and the control group that will receive the foot SM.

Randomization will be established by the MeDatas cell of the Clinical Investigation Center (CIC). When a subject is included, the assignment of a number and group will be established by means of a secure randomization interface via the CIC website.

Subjects will be randomized once the investigator verifies that they meet the eligibility criteria (Section 5). Patients will be randomized to one of 2 groups according to the chronological order of inclusion of patients in the protocol.

Randomization will be done at the inclusion visit. Only the person in charge of foot reflexology and sham massages ([name]) will be informed of the patient's randomization.

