## INCLUSION VISIT / RANDOMIZATION PROCESS

### Collection of consent

Prior to any research-related review, the investigator obtains the free, informed, and written consent of the participant (or his/her legal representative if applicable).

If the participant gives his or her consent to participate, the participant and the investigator write their first and last names in plain text, date and sign the consent form. This must be signed BEFORE CARRYING OUT ANY CLINICAL OR PARACLINICAL EXAMINATION REQUIRED BY THE

RESEARCH. The consent is signed in 2 copies, one of which is delivered to him in person.

Once eligibility has been verified and consent has been signed, randomization can take place. When an investigator wishes to perform randomization after verifying the participant's eligibility, they log on to the website: http:// XX . The investigator completes the "randomization" web page after having previously confirmed all the patient's eligibility criteria on the site. After validation of the content, randomization is performed and the site immediately communicates to the investigator the unique number of the participant in the research, the result of the randomization, in particular the procedure group allocated to the patient.

Following randomization, each participant will benefit from an evaluation at inclusion:

- **Socio-demographic data (age, sex).**
- **PD treatments, analgesic treatments and concomitant treatments in progress.**
- **Pain that includes:**
  - The maximum and average VAS over the previous week *[Price 1994]*
  - The KPPS: a scale that assesses the intensity of pain in PD *[Chaudhuri 2015]*
  - The BPI *[Brasseur 1997]* - The Mac Gill *[Turk 1985]*
  - CPAQ-8: a questionnaire that assesses the extent to which the person "accepts" the presence of pain *[McCracken 2004]*
  - 3 PDQ (Parkinson's Primary Pain Questionnaire)
- **Motor state, anxiety and depression which include:** - The MDS UPRDS III scale *[Defebvre 2018]*

- HAD (Hospital Anxiety and Depression) scale *[Lépine 1985]*

- **the intensity of the pain thanks to the VAS before each FR vs SM session (from V1 to V4) over the last 7 days,**
- **an assessment of the subjective pain perception threshold and heat tolerance via the thermotest before and after the FR vs SM session**
- **An assessment of the personality profile using the TCI personality questionnaire.**

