The 15 patients in each group will benefit from an fMRI before the first session of FR vs SM at the Baudot technical platform.

**Following all these evaluations, the patient will benefit from the 1st session of PR, or MS, performed by the reflexologist.**

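### The personality analysis names a Mann-Whitney test without linking the TCI to the pain response; in its usual FR-versus-SM use here it would only check baseline balance

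*Protocol*

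**What the plan says.** Protocol section 3 (Secondary objectives, last item) sets the question: "To assess whether there are personality traits that modulate the analgesic response in the 2 groups of patients". Section 4 (Secondary outcomes, last item) gives the matching outcome: "Comparison between the 2 groups of patients of their analgesic response according to their personality profile".

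The analysis is a single line, the last of the numbered secondary items in section 11 (Statistical methods used): "Personality profile results will be analyzed using a nonparametric Wilcoxon Mann Whitney test". It does not say what is compared, between which groups, or how pain enters.

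The summary table in section 9 schedules the TCI at V1 only. The inclusion-visit text lists "An assessment of the personality profile using the TCI personality questionnaire" among the V1 evaluations and then says "Following all these evaluations, the patient will benefit from the 1st session of PR, or MS, performed by the reflexologist". The TCI is therefore a pre-treatment variable with no later value and no change score.

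On how the protocol uses this test, section 1 lists it under comparisons between the two groups: "The non-parametric Wilcoxon Mann-Whitney test will be performed for quantitative variables". Section 11 applies it in the same FR-versus-SM sense to the primary outcome and to the visit-by-visit VAS changes. Allocation is randomised (section 5): "Patients will be randomized into two groups in a 1:1 ratio".

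**The concern.** Modulation involves three quantities: the trait, the pain response and the arm. A Mann-Whitney test compares one variable between two groups. If the variable is the TCI score and the groups are FR and SM, pain change is absent and the test only asks whether randomisation happened to balance personality. A significant result would be a chance imbalance, yet it could be reported as a personality effect on analgesia. A non-significant one would say nothing about modulation. A stated secondary objective would then go unanswered although the data for it are collected.

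**Working it through.** **Side by side.** The objective and outcome concern analgesic response as a function of personality, in and between the two groups. The analysis line concerns personality results and a two-sample rank test. The link between trait and VAS change is missing.

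**Why the FR-versus-SM reading carries no information.** The test statistic depends only on the ranks of the trait and the arm labels. The TCI follows randomisation but precedes the first session, so with patients blinded to arm its distribution is the same in both arms. The rejection probability is then about alpha = 0.05, whatever the dependence of VAS change on the trait.

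**Inputs.** The personality analysis has no figure of its own. The sample-size paragraph in section 11 gives a 20 mm difference (2 points on 0-10), an SD of 1.5 (taken as 0-10 points), two-sided alpha 0.05, beta 0.20, 12 per group needed and 15 recruited. As a check on these inputs:
- Normal approximation: 2 × (1.5 × (1.960 + 0.842)/2)² = 8.83, so 9.
- Two-sample t-test: 9.89, so 10.
- Dividing by 0.864, the minimum efficiency of the rank test: 9.89/0.864 = 11.4, so 12. This is one route to the stated figure; the protocol does not give its own.
- 12 × 1.25 = 15.

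**Simulation** (6,000 runs per setting, two-sided 0.05). The trait is standard normal and randomised 1:1. Improvement in VAS = 2 × arm + b × trait × arm + N(0, 1.5), so the trait acts in FR only. Baseline VAS is N(6, 1.2), limited to 4-10, and is used only to define a 30% responder. The interaction model contains arm, trait and their product. The values of b (VAS points per trait SD), the baseline distribution and the FR-only form are assumptions; the protocol gives none of them.

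Percentage of runs that reject:

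| b | TCI, FR vs SM (15 / 12 per arm) | TCI, responders vs non-responders, both arms pooled (15 per arm) | Same, within FR (15 per arm) | Arm-by-trait interaction (15 / 12 per arm) |
|---|---|---|---|---|
| 0 | 4.2 / 4.4 | 4.5 | 3.8 | 5.1 / 5.0 |
| 0.75 | 4.0 / 4.9 | 15.3 | 19.9 | 22.9 / 19.4 |
| 1.5 | 4.5 / 4.3 | 34.2 | 56.0 | 67.9 / 56.1 |
| 2.25 | 4.6 / 4.5 | 49.5 | 80.9 | 93.4 / 85.8 |
| 3 | 4.4 / 4.3 | 59.0 | 91.8 | 99.3 / 96.6 |

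The between-arm TCI test stays at its nominal level throughout. The responder comparison reacts to modulation but does not contrast FR with SM. The interaction test does contrast them, with useful power only when modulation is large: b = 1.5 is 15 mm per trait SD, or 1.5/2 = 75% of the 20 mm design difference. The reading by profile stratum was not simulated.

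**The case against.** The strongest reply is that the analysis line names neither groups nor variable, so the FR-versus-SM comparison of TCI scores is an inference. Read with the outcome it serves, the line could mean VAS change compared between arms within profile strata, or TCI scores in responders versus non-responders. The objective, which speaks of modulation in the two groups, might even be met by within-arm analyses. Details such as the TCI dimensions and the definition of a profile may properly sit in a statistical analysis plan.

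Much of this stands. A reader might infer that the objective cannot be answered at all, or that power can never exceed alpha. The protocol does not support that: both statements hold only for the FR-versus-SM reading of TCI scores, and the table shows the responder reading picking up an association.

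A reader might also cite an inflated false-signal rate. With an assumed 4 to 7 independent scales it would be 1 − 0.95⁴ = 0.185 to 1 − 0.95⁷ = 0.302. The protocol states neither the number of scales nor their independence, and the same arithmetic applies to interaction tests run scale by scale, so it does not separate the planned analysis from a better one.

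What does not stand is that this is only missing detail. The protocol fixes a test, uses it elsewhere for FR versus SM, and on none of these readings does that test estimate how trait dependence differs between arms, which is what the outcome describes.

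**Conclusion.** The point holds in this form: the named test is not tied to the VAS response, and in its ordinary use in this protocol it would check baseline balance and nothing else, rejecting about 5% of the time per scale at any strength of modulation. That figure rests on randomisation, on the TCI preceding treatment and on patient blinding, not on the assumed values of b. The unstated alternatives could show an association but would not compare modulation between FR and SM. The primary analysis is unaffected. This is one secondary objective of a 30-patient exploratory study, worth correcting because the correction uses data already collected.

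**What to change.** Replace the line in section 11 with a statement that links trait to response. For each TCI dimension, model V5 VAS on arm, V1 VAS, trait score and arm-by-trait interaction. Report the interaction and the trait slope within each arm, all with 95% confidence intervals. To stay with rank methods, a lighter option is the Spearman correlation of trait with the V1-V5 VAS change within each arm, with confidence intervals. Drop any between-arm test of TCI scores; a descriptive baseline table is enough. State that these are exploratory estimates over several scales without multiplicity adjustment.

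The cost is a wording change and a few more model runs, with no change for patients. The linear model departs from the rank-based analysis of raw changes used elsewhere in section 11, which the Spearman option avoids. With 12 to 15 per arm the estimates will be imprecise: simulated interaction power is 19% to 23% at 0.75 points per trait SD and 56% to 68% at 1.5. Intervals should therefore carry the message rather than p-values.
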